##### Survey and data collection

The survey questions were developed using Australian Bureau of Statistics tools (the 2012 Waste Management questions and the 2014–2015 National Health survey [21, 26]), relevant literature [19, 22], and input from the NatRUM Ltd. Board (available on request from correspondence author).

The survey is designed to take around 10 min to complete. The questions have multiple-choice options with a free-text response available when the ‘other’ option is selected. It consists of:11 demographic questions (e.g. age, gender, state/territory, country of birth, language spoken at home, living arrangements, education, employment, household income);Four questions on whether respondents currently have unwanted (used, unused or expired) medicines in their home, the type of medicines retained (prescription, OTC, complementary and/or alternative) and why they have retained them;Three questions on disposal practices (whether respondents have disposed of any in the last 12 months, how they disposed of them and why). The questions on disposal practices have been included from the Australian Bureau of Statistics with minimal changes to allow for comparison of results [21];Two questions on awareness and use of the NatRUM scheme. Respondents who are not aware of the NatRUM scheme are provided with a brief overview of the scheme, and a link to the website (www.returnmed.com.au), and asked if they would use the national scheme in the future:Respondents are also asked to indicate whether they are healthcare workers, with a further four questions relating to the advice they give to their patients about medicines disposal.

Finally, two ‘ranking’ questions will assess a potential social marketing strategy designed to inform better use of the NatRUM program. The first question relates to concerns about storing and disposing of unwanted medicines, the second addresses the best media for the promotion of associated public health messages. In the online version of the survey the order of response options for these two questions will be randomised. Survey respondents will be asked to rank the statements in order of most important/effective to least important/effective.

The survey has been piloted (in hardcopy) with two members of the NatRUM Ltd. Board and seven people from the general population with medicines in their homes who were known to the research team. Minor amendments to the wording and question order were subsequently made.

Working with Research Now®, a user-friendly survey which could be completed on-line, or using mobile devices such as smartphones, was developed. For all questions with six or more multiple-choice options the option list is randomised. The online survey has been soft-launched with 48 panel members to test the response algorithms. For the survey proper, Research Now® will invite participation from its panel members to ensure good sample representation and adjust when necessary to ensure targets for under-represented groups (e.g. younger people) are met for the survey sample (*n* = 4300). Survey respondents will be provided with compensation for their time in accordance with terms of their enagagement with Research Now®.

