### Dissemination and projected impact

This cross-sectional study aims to explore the current use of the National Return of Unwanted Medicines scheme and provide further insight about practices and awareness from the general public and healthcare workers about the scheme, and their attitudes towards the storage and disposal of unwanted medicines. It is anticipated that this study will provide evidence about the level of knowledge held by a representative sample of adult Australians, particularly in relation to appropriate disposal practices for unwanted medicines stored at home. It will provide initial insights into the variable risk perceptions, risk assessment strategies, and medicines use and disposal behaviours amongst consumers, with implications for quality use of medicines and risk of harm.

The study will ultimately reveal opportunities for national and grassroots information campaigns in raising awareness of the NatRUM scheme and the environmental, economic and public health risks associated with inappropriate medicines disposal and accumulation of unwanted medicines at home; targeting healthcare workers and members of the general population, particularly for those who use, or care for people who use, multiple medicines. To ensure the effectiveness of such campaigns it is important that they are informed by input from stakeholders such as consumer and carer organisations, and align with existing quality use of medicine campaigns. In Australia this includes examples such as: the National Prescribing Service’s *Be Medicinewise* week [29]; the Pharmacy Guild of Australia’s *Ask Your Pharmacist* consumer campaign [30]; or the *Choosing Wisely Australia* initiative [31]. These strategies will ideally encourage people to regularly check and clean out their medicines, limit inappropriate medicines use and/or accumulation, and promote appropriate medicines disposal.

In order to support the translation of findings into the anticipated outcomes described here, the research team plan to disseminate findings in late 2017/2018 in scientific journals, at national meetings (e.g. those with a pharmacy, primary care, and drug safety/quality use of medicines focus), and with pharmacy and healthcare media.

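### As listed, healthcare workers unaware of the scheme read an overview of it before reporting the advice they give patients, which may bias that advice upward

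*Protocol article*

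**What the plan says.** The Protocol article (Stage two, Step one, *Survey and data collection*) outlines the survey block by block: demographics, unwanted medicines in the home, disposal practices, and then "Two questions on awareness and use of the NatRUM scheme". Within that last block, "Respondents who are not aware of the NatRUM scheme are provided with a brief overview of the scheme, and a link to the website", and they are asked whether they would use the scheme in future.

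The next item is the healthcare-worker screen: "Respondents are also asked to indicate whether they are healthcare workers". Attached to this screen are the advice items, which the article introduces in these words: "with a further four questions relating to the advice they give to their patients about medicines disposal". The following paragraph opens "Finally, two ‘ranking’ questions will assess a potential social marketing strategy".

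The same section reports a change after the pilot: "Minor amendments to the wording and question order were subsequently made". It says the questions can be had on request, and that response options are randomised for longer lists and for the ranking questions. It mentions no randomisation of question blocks. The Step one *Data analysis* section plans mainly descriptive analysis.

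On purpose, *Dissemination and projected impact* says the study will "provide further insight about practices and awareness from the general public and healthcare workers about the scheme" and foresees information campaigns aimed at healthcare workers among others.

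**The concern.** An explanation of the scheme placed just before a self-report of practice on the same subject can hint at the desirable answer. Here the exposure is also selective: only respondents who have just said they are unaware see it. Any contamination therefore falls on workers whose unprompted practice is of most interest, and it makes them look more like aware workers.

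The outline treats the two practice measures differently. Respondents' own disposal practices are listed before the overview and so are shielded from it. The advice items, which are the practice measure specific to healthcare workers, are listed after it.

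At stake is the reading of current advice. If reported advice is too favourable among the unaware, the case for informing healthcare workers looks weaker than it is. Once the overview has been shown, no analysis can recover what an unaware worker would have answered without it.

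**Working it through.** **1. Order.** The article gives no figure to reproduce, so the first check is the sequence. In the order of the outline:

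1. Demographics
2. Unwanted medicines at home
3. Own disposal practices in the last 12 months
4. Awareness and use of the scheme (two questions)
5. For the unaware only: overview, website link, future-use question
6. Healthcare-worker screen, then four advice questions for workers
7. Two ranking questions, introduced by *Finally*

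A list that starts with demographics and closes with *Finally* reads most naturally as survey order. On that reading the awareness questions (4) precede the overview (5) and are clean, while the advice items (6) follow it. Nothing in the article says that the advice items are protected from the overview.

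**2. Possible size.** Every input here is an assumption, because the article gives none of them:

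- u: share of healthcare workers unaware of the scheme
- c0: true share of unaware workers who already give the desired advice
- s: share of the remaining unaware workers who change their reported answer after the overview

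Bias among the unaware = s × (1 − c0). Bias among all healthcare workers = u × s × (1 − c0). The aware-unaware difference narrows by s × (1 − c0), provided the aware group's true share is the higher by at least that much.

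| u | s | c0 | Unaware workers (points) | All workers (points) |
|---|---|---|---|---|
| any | 0 | any | 0 | 0 |
| 0.1 | 0.1 | 0.2 | 0.1 × 0.8 = 8 | 0.1 × 8 = 0.8 |
| 0.3 | 0.25 | 0.2 | 0.25 × 0.8 = 20 | 0.3 × 20 = 6 |
| 0.5 | 0.5 | 0.2 | 0.5 × 0.8 = 40 | 0.5 × 40 = 20 |
| 0.5 | 0.5 | 0.6 | 0.5 × 0.4 = 20 | 0.5 × 20 = 10 |

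**3. Sampling error for comparison.** Suppose healthcare workers are 5% to 10% of the 4300 respondents (assumed), that is 215 to 430. The 95% half-width at a proportion of one half is 1.96 × √(0.25/n): 6.7 points at n = 215 and 4.7 points at n = 430. If 40% of them are unaware (assumed), the unaware group has 86 to 172 people and half-widths of 10.6 to 7.5 points. Bias in the unaware should be set against this second pair of half-widths. At s = 0.1 and c0 = 0.2 the bias (8 points) is about the size of the sampling error; at s = 0.5 it is well above it.

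**4. After reordering.** If the advice items come before the overview, s = 0 for this route and the bias by this route is 0 whatever u and c0 are.

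**The case against.** **The order is not stated.** The outline describes what the survey contains, the healthcare-worker screen is attached by *also* rather than *then*, and *Finally* strictly places only the ranking questions. Question order was amended after piloting, and an article may fairly leave the exact order to the questionnaire. This stands. It makes the first step a request for confirmation, although nothing in the article suggests that the amendment moved the advice items.

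**The effect is not shown.** A reader might infer that reported advice is inflated. The document does not support that. The wording and options of the four questions are not given, so it is unclear how far they have a desired answer. They ask about advice that workers already give. An unaware worker may answer truthfully, or may already advise return to a pharmacy without knowing the scheme. Only a risk of upward bias can be claimed.

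**The importance is limited.** Advice to patients is not among the Stage Two objectives in *Study design overview*. The *Background* and *Dissemination and projected impact* name practices and awareness of healthcare workers without mentioning advice, and no aware-unaware comparison of advice is planned in the article. This also stands. It lowers the weight of the point but does not remove it: the four questions are asked in order to describe what workers advise, and their answers should be free of a prompt from the survey itself.

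**Moving the items too far forward has a price.** Disposal-advice questions placed ahead of the awareness question could prime awareness, which is a stated objective. This is correct and determines where the items should go.

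**Conclusion.** The point holds as a risk that depends on the programmed order. As the article lists the survey, unaware healthcare workers meet the overview before the advice questions, and no safeguard is described. Their reported advice may be biased upward and the aware-unaware difference narrowed.

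The size is unknown. The illustrations of 0 to 20 points among all healthcare workers and 0 to 40 points among the unaware rest wholly on assumed values of u, s and c0, and the lower end is no bias at all.

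Two further inferences should be resisted. The awareness estimate is not contaminated, because awareness is asked before the overview. Nor would confining practice conclusions to aware workers be a sound answer: it selects on knowledge of the scheme and could itself overstate good practice among all workers.

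The absence of a split by prior awareness in the article is not held against it, since such detail may sit in a fuller plan. The point rests on the listed order.

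**What to change.** 1. Confirm the order as programmed in the online survey, and state it in the article or with the questionnaire.
2. If it is as listed, use this sequence: awareness and use questions; healthcare-worker screen and four advice items; overview, website link and future-use question for the unaware; ranking questions. Awareness is then asked before any advice item, and advice before any overview. The awareness question itself still comes ahead of the advice items, but aware and unaware workers meet it alike.
3. If the order can no longer be changed, report advice separately for workers aware and unaware at the awareness question, and flag the unaware workers' answers as given after the overview. Keep both groups in any description of practice.

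The cost is a change of block order and a short re-test of the routing. The article describes a soft launch with 48 panel members and main fieldwork still to come, so the change looked feasible at the time of writing. It adds no questions, respondents or interview time, and no stated sample size changes. The fallback costs one extra table split and a footnote.

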##### Data analysis

All survey responses will be provided by Research Now® in a de-identified Microsoft Office Excel® spreadsheet. Data analysis will be performed using Microsoft Office Excel® 2007 and Stata® v.13. Statistical analyses will be descriptive in nature for the majority of questions. The ranking questions containing the social marketing statements will be analysed using a rank-order logit regression [27], with robust standard errors to mitigate against unknown specification errors. As sociodemographic variables do not vary across the set of possible rankings, and therefore cannot be identified as main effects, interactions with key sociodemographic variables will be tested for joint significance and included in the final model if they reach statistical significance (*p* = 0.05).

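### The ranking models keep sociodemographic interactions only if they reach p = 0.05, so the final model is chosen by the data that supply its p-values and intervals, and robust standard errors do not mend a misspecified model

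*Protocol article*

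**What the plan says.** In the protocol article (Stage two, Step one, Data analysis), most survey questions are to be described only. The exception is the pair of ranking items: "two ‘ranking’ questions will assess a potential social marketing strategy". They are to be analysed by rank-order logit "with robust standard errors to mitigate against unknown specification errors". Sociodemographic variables can enter only as interactions with the ranked items. The rule for them is that "interactions with key sociodemographic variables will be tested for joint significance and included in the final model if they reach statistical significance", with the cut-off set at p = 0.05.

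The article does not name or count the key variables. The section Survey and data collection gives the pool: "11 demographic questions (e.g. age, gender, state/territory, country of birth, language spoken at home, living arrangements, education, employment, household income", among others.

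The same section describes the awareness block, in which "Respondents who are not aware of the NatRUM scheme are provided with a brief overview of the scheme, and a link to the website". The ranking items are then introduced as the closing part of the survey. Of these, "The first question relates to concerns about storing and disposing of unwanted medicines", and the second concerns media for promotion. The order of response options within each ranking is randomised.

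**The concern.** Three features bear on how far a subgroup difference in these rankings can be trusted.

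- **Selection.** A term that stays in the model only when it passes 0.05 is reported on condition that it looked large. Its estimate is then exaggerated on average, and its p-value and interval ignore the selection. A term that fails is set to zero, which reads as no difference.
- **Robust variance.** The article presents robust standard errors as a guard against specification error. In a non-linear model such as the rank-order logit, a wrong specification moves the coefficients themselves. A sandwich variance gives a more honest standard error around whatever value the model converges to, but does not bring that value back.
- **Unequal information.** If the rankings follow the overview, unaware respondents rank their concerns just after reading about the scheme, and aware respondents do not. Randomising response options does not balance that.

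At stake is whether differences between age, language or education groups in what they rank highest are real. They could instead be products of the selection rule, of differing ranking noise or of question order.

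**Working it through.** **Inputs**

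- Retention threshold: 0.05 per joint test (Data analysis). This is a chosen cut-off, so there is no derived figure to reproduce. The article gives no power, effect size or overall error rate for these models.
- Outcomes: 2 ranking questions (Survey and data collection).
- Candidate variables, k: not stated. The upper limit is the 11 demographic questions; 3 and 5 are assumptions.
- Survey size: 4300 (Participants).

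**Chance of a false retention.** Joint testing most naturally means one test per variable, across all ranked items, so the number of tests is m = 2k. It could also mean one omnibus test per question, so m = 2. With no true interactions and independent tests, P(at least one false retention) = 1 − 0.95^m. The expected number of false retentions is 0.05m, and the first Holm threshold is 0.05/m.

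| Reading | m | P(at least one) | Expected number | First Holm threshold |
|---|---|---|---|---|
| One omnibus test per question | 2 | 1 − 0.95^2 = 9.75% | 0.10 | 0.025 |
| 3 variables | 6 | 1 − 0.95^6 = 26.5% | 0.30 | 0.0083 |
| 5 variables | 10 | 1 − 0.95^10 = 40.1% | 0.50 | 0.005 |
| All 11 items | 22 | 1 − 0.95^22 = 67.6% | 1.10 | 0.0023 |

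For one question alone, 3, 5 and 11 variables give 14.3%, 22.6% and 43.1%. Demographic items are related to one another, so independence is an approximation. The expected numbers do not depend on it.

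**Robust standard errors.** Rank-order logit data were simulated 300 times per setting at N = 4300. The assumptions were 5 ranked items with utilities 0, 0.2, 0.4, 0.6 and 0.8, one binary covariate splitting the sample evenly, and a robust Wald joint test of the interactions at 0.05.

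- Correct model, no interaction: 5.7% rejected. This agrees with 5%, since the simulation standard error is √(0.05 × 0.95/300) = 1.3 percentage points.
- Same relative preferences, one group's utility scale at 0.9 of the other's (noisier ranking): 22% rejected.
- Same, with scale 0.8: 75% rejected. The mean interaction coefficients were −0.036, −0.074, −0.116 and −0.159.

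In such a model a coefficient mixes strength of preference with consistency of ranking. A difference in consistency therefore appears as an interaction although both groups hold the same relative preferences, and the robust variance does not prevent it. The scale factors are illustrative; nothing in the article indicates their size.

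**Question order.** The sequence in the article's list is: awareness and use of the scheme; overview, website link and future-use question for the unaware only; healthcare-worker items; and last the two rankings. No effect size can be computed from this. The overview would distort demographic interactions only if awareness differs across demographic groups and reading the overview changes rankings. Neither is documented.

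**The case against.** The strongest reply is that this is an ancillary analysis in a condensed article. The ranking questions are not among the four Stage Two objectives in Study design overview. The list of key variables and any multiplicity handling may sit in a fuller plan that is not shown, and their absence from the article is no fault. Testing jointly already limits multiplicity within a variable. Calling all 11 items key strains the word. No misspecification has been shown for these data. The questionnaire and the overview text are not shown, so the screen order is inferred from a list. Aware respondents already know of the scheme, so a brief overview might narrow the information gap.

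Most of this stands, and it limits the point. It does not answer the retention rule, which the article states outright: naming the variables elsewhere would leave inclusion dependent on p-values. Nor does it rescue the claim made for robust standard errors, which is a matter of method and not of these data.

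A reader might infer more than the article supports in three ways:

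- That 40% or 68% is the plan's error rate. Both rest on an assumed number of independent tests; one omnibus test per question gives about 10%.
- That these models will drive messages aimed at demographic subgroups. The article says only that the rankings assess a potential strategy. Dissemination and projected impact names healthcare workers and the general population, particularly people who use multiple medicines or care for those who do. It does not name groups found by the model.
- That the rankings of unaware respondents are primed. The routing makes this possible, but its size and direction are unknown.

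**Conclusion.** The concern holds for the selection rule and for the claim made for robust standard errors. Interactions retained at p = 0.05 over two ranking questions will tend to be overstated, with intervals that are too narrow. The chance of at least one false retention runs from about 10% to 68%, depending on the number of tests, if no true interactions exist and the tests are independent. The robust standard errors address uncertainty only, so the stated purpose is too broad. The question order is a reason for a cheap precaution and is not a demonstrated bias. The consequence is confined to subgroup conclusions from the ranking models. The bin audit and the descriptive estimates of awareness, disposal practice and stored medicines are not affected.

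**What to change.** - **Interactions.** Before analysis, fix a short list for both questions. Keep and report all of them with joint tests and intervals, whatever their p-value. Apply Holm adjustment across variables and both questions, and label the subgroup results exploratory.
- **Robust standard errors.** Keep them, but narrow the stated purpose to the uncertainty of the estimates.
- **Sensitivity analysis.** Always report a first-choice-only refit and a top-three refit beside the full-ranking model. Do not choose between them on the results, since that would be another data-dependent selection.
- **Question order (precaution).** Show the overview and the future-use question after the rankings. If the online form cannot be changed, include awareness status as an interaction.

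The cost is somewhat wider intervals, a few extra model runs and revised analysis wording. A change of screen order also needs reprogramming and retesting, because the form has already been soft-launched with 48 panel members.
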